# Appendix D: UNSW Safety Monitor Register Template

| **Section 1: Project Details** | | | | | | |
| --- | --- | --- | --- | --- | --- | --- |
| 1. **HREC/HREAP reference number:** |  | | | | | |
| 1. **Project title:** |  | | | | | |
| 1. **Chief Investigator** |  | | | | | |
| 1. **Approving HREC:** |  | | | | | |
| 1. **Type of report** | **Initial**  **Follow up** | | | | | |
| **Section 2: Details of the event** | | | | | | |
| 1. **Date of occurrence** |  | | | | | |
| 1. **Location of occurrence** |  | | | | | |
| 1. **Has the event or incident been resolved** | **Yes**  **No** | | | | | |
| 1. **Who was affected by the event or incident** | **Party Affected** | **Yes** | **No** | **If yes, provide further detail such as number of participants/records, names of researchers etc.** | | |
|  | Research Participants |  |  |  | | |
|  | Researchers |  |  |  | | |
|  | Research Records, Data or Property |  |  |  | | |
| 1. **Did the event result in or cause any of the following?** | - Death - Life-threatening - Hospitalisation - Prolongation of existing hospitalisation - persistent or significant disability or incapacity - congenital anomaly or birth defect | | | | | |
| 1. **Describe the incident using lay language. Include details of any negative consequences, harm or damage that has occurred because of the incident.** | | | | | | |
| 1. **What has been identified as the cause of the incident?** | | | | | | |
|  | | | | | | |
| 1. **Describe the corrective steps that have occurred and those that are to occur following this report.** | | | | | | |
|  | | | | | | |
| 1. **Describe the preventative steps to stop reoccurrence.** | | | | | | |
|  | | | | | | |
| 1. **Has the event/incident had an impact on the ethical acceptability of the research** | | | | | **Yes** | **No** |
| 1. **Was the event/incident related to the study design and / or procedure?** | | | | | **Yes** | **No** |
| 1. **Was the event/incident anticipated in the in the risks section of the approved project description?** | | | | | **Yes** | **No** |
| 1. **Will the event/incident adverse event raise additional safety concerns for the participants of this research or affect participants’ willingness to continue participation** | | | | | **Yes** | **No** |
| **Section 3: Declaration** | | | | | | |
| By submitting this form, I Chief Investigator declare that:  The information contained in this report is true and accurate. | | | | | **Yes** | **No** |

# Appendix E: Data and Safety Monitoring Board Charter

**The LifeBuoy Study: Data and Safety Monitoring Board Charter**

**Study Overview**

**The LifeBuoy App: A superiority randomised controlled trial of a mHealth intervention to help young people manage suicidal thoughts**

| Sponsor: | University of New South Wales, Sydney |
| --- | --- |
| HREC Reference number: | HC190764 |
| Clinical Trial Notification Number: | CT-2020-CTN-00256-1-v1 |
| Clinical Trials Registration Number: | ACTRN12619001671156 |
| Number of Sites: | National |
| Number of Participants: |  |

# Data and Safety Monitoring Board (DSMB) Overview

**DSMB Description**

- This DSMB members will have a degree of independence from the Black Dog Institute, University of New South Wales Sydney, and investigators, as required by the NHMRC for non-commercial trials.
- This charter will be approved by its DSMB members.
- The DSMB will function in accordance with the principles of the following documents: Good Clinical Practice (GCP) Guidelines, Declaration of Helsinki 2000, NHMRC National Statement on Ethical Conduct in Human Research, NHMRC Guidance Safety and Monitoring of Clinical Trials involving a Therapeutic Good, and University of New South Wales HREC guidelines.

**DSMB Membership Conflicts of Interest & Composition**

- Members will disclose conflicts of interest and will be cleared of significant conflicts of interest and potential conflicts of interest. No member should have financial, proprietary, professional, or other interests that may affect impartial, independent decision-making by the DSMB.
- Composition of membership will reflect exptertise in clinical trials (including a good understanding of the problems and limitations of trials), statistics and the specific scientific expertise relevant to the study, in this case, the suicidality in young people. Members will comprise 3 individuals with expertise in these areas.
- A quorum group of two must be present for closed sessions and subsequent decisions and/or recommendations made by the committee.

**Reporting**

- Data requiring review by the DSMB will be provided by the Trial Manager ([name]) for the open session, and the data officer ([name]) for the closed session.
- Issues and recommendations identified by the DSMB will be provided to Trial Steering Group (TSG), comprising the Trial Lead and Chief Investigator ([name]), the Trial co-lead and Investigator ([name]), the Trial Manager ([name]), and the co-Chief Investigators ([name], [name], Assoc [name] and [name] [name], [name]) by the DSMB in accordance with this charter.

#

**Study Summary**

Involving young people aged 18 – 25 years from the Australian general community, this randomised controlled trial (RCT) will examine the use of a smartphone application (‘LifeBuoy’) to deliver digital Dialectical Behaviour Therapy (DBT) and Acceptance and Commitment Therapy (ACT) to reduce symptom severity of suicidal ideation. This study will rely on self-report data to evaluate the efficacy of the app. This study is funded by the Roth Family Foundation and an Australian Rotary Health Youth Mental Health Grant for 2 years.

**Design**

A randomised-controlled, double-blind, superiority trial with two-parallel arms (intervention and attention-matched control) with 1:1 allocation. Assessment and study procedures are automated and so the risk of differential treatment of those in the intervention and control is minimised.

**Objectives**

1. To assess the efficacy of the LifeBuoy app in reducing suicidal ideation in young people, as measured by the Suicidal Ideation Attributes Scale. Changes in suicidal ideation will be assessed by comparing the intervention and attention placebo control conditions at baseline and post-intervention, and 3-month post intervention follow-up.
2. To assess whether the LifeBuoy app significantly reduces depression and anxiety symptoms at post-intervention relative to the placebo attention control condition.
3. To examine the adherence (no. modules completed) and acceptability of the LifeBuoy app among intervention condition participants.
4. To identify predictors of change in suicidal ideation outcomes.

**Investigational Products**

**LifeBuoy.** The Lifebuoy app is a mobile app developed by researchers at the Black Dog Institute. It is a fully automated, self-help program for young people experiencing mild-to- moderate symptoms of suicidal ideation. The app has been developed using a person-centered approach, to understand and accommodate the perspectives of young people who will use the intervention. Participants will download the app from the App Store or Google Play onto their personal smartphones. Once the app is downloaded, it will not require internet connection; internet connectivity will only be required to upload usage and adherence data to UNSW servers. The app contains seven learning modules derived from Dialectical Behaviour Therapy (DBT) and Acceptance and Commitment Therapy (ACT) and incorporates wise mind principles (distress tolerance, emotion regulation/mindfulness, interpersonal effectiveness) through interactive learning exercises to help young people develop strategies and skills for managing distress. Participants have 6 weeks to complete the seven modules, each which takes approximately 3 - 5 minutes to work through. The user will be directed to each module linearly, and when an island is complete it becomes coloured to show that the user has already visited it.

**Follow-up Schedule**

All participants will complete self-report questionnaires at baseline, six-weeks post-baseline (post-intervention), and follow up. We will also conduct qualitative interviews with n=20 participants in the intervention condition at the end of the recruitment period to assess their experience of using the app. Participants will be recruited into the qualitative interviews at the start of the final assessment.

**Roles and Responsibilities**

As outlined by NHMRC Guidance on “Safety monitoring and reporting in clinical trials involving therapeutic goods” (2016), the roles of the DSMB will be to assist in:

- safeguarding the interests of study participants
- ensuring that definitive and valid results are produced which will reliably inform future healthcare decisions
- enhancing the credibility of the trial.

These roles will be achieved by examining the data accumulated during the progress of the trial, ensuring risks and benefits are monitored, and that the trial remains safe for participants. The role of the committee is to review data completeness, adverse events, outcome data (unblinded if there is good reason for this) and to recommend to the trial committee whether the study requires modification.

Recommendations will be made to the TSG, which, if appropriate, will be shared by the trial team with the Sponsor and the HREC.

**The DSMB will:**

- Following each assessment point, review aggregate subject data related to safety, attrition, withdrawals, data integrity and overall conduct of the trial and discuss via telephone conference;
- Provide recommendations to continue, modify or terminate the trial;
- Maintain records of all activities.

**The Investigators will:**

- Assure the proper conduct of the study according to the study protocol and relevant research guidelines;
- Assure collection of accurate and timely data;
- Compile and report data for the DSMB report at the end of each assessment period (trial manager and data officer);
- Monitor the project email inbox;
- Promptly report potential safety concern(s) to the DSMB;
- Communicate with regulatory authorities, e.g. HREC in a manner that maintains integrity (e.g., blinding) of the data, as necessary.

**Selection of the Chair**

The Chair should have previous experience of serving on a DSMB and experience of chairing meetings, and should be able to facilitate and summarise the DSMB discussions.

**DSMB Meetings**

The first meeting

The members should review this charter and form an understanding of the protocol and study endpoints. Meetings will take place at an appropriate regularity decided by the DSMB committee. The DSMB will also meet if evidence from other research groups suggests potential for risk.

Meeting formats

DSMB meetings will be booked in for the week following the completion of data collection at each assessment point of the trial (baseline, post-intervention, 3-month post-intervention follow-up). Procedurally, when these set meetings are booked they will include both an open and closed session, however, it is up to the DSMB to decide if they would like to have a closed session. The typical structure of the meetings will first start with an open session involving both DSMB members, the trial leads, and the trial manager, followed by the closed session if needed. The meetings will be organised and chaired by either MT or JH. These meetings will generally be conducted by teleconference or videoconference, but the DSMB can decide whether they would like to do this face-to-face.

In the event of a closed meeting, unblinded data may be requested if there is a rationale (e.g. unexpected adverse events, aggregate data indicates self-harm above the rates expected from this group). Only DSMB members and others whom they specifically invite are present in closed meetings.

Outside of the pre-scheduled meetings, an extraordinary meeting may be called if a serious adverse event occurs. The trial leads or trial manager will report the event to the Chair within 24 hours of becoming aware of the event, and the Chair will convene a closed session meeting to discuss the event and make recommendations.

Following each meeting, a report minuting the open session including any DSMB recommendations and rationale for such will be prepared by the minute taker and sent to the CIA (MT) and all other members. For closed sessions, recommendations will be prepared by the Chair and sent to the Trial Lead (MT), who will present the outcomes at the TSG following each meeting. Meetings will occur until the trial concludes.

Reporting

In terms of expedited reporting of events to the DSMB in between its regular sessions, the process will be guided by the NHMRC ‘Risk-based Management and Monitoring of Clinical Trials Involving Therapeutic Goods, 2018’, bearing in mind that this is a trial of an mhealth preventive intervention and not a medicine or treatment. The trial is regarded as being in the lowest risk category, type A, with risk comparable to standard medical care. All Serious Adverse Events (SAEs) will be regarded as non-expedited (ie. only to be reported at the next DSMB meeting), unless the SAE is both unexpected and possibly related directly to participation in the trial, in which case it will be reported to the DSMB via email within 24 hours as well as other agencies. For this 6-week low intensity app-based DBT intervention, it is anticipated that all SAEs that are possibly related to trial participation will be reported. In the event of uncertainty, the TSG should default to reporting the SAE to the DSMB.

Responsibilities of the Data Officer

The data officer will be responsible for producing the closed session report to the DSMB, and assist the trial manager with the open session report. The main purpose of this role is to ensure that the Investigator team remain blind to study outcome data. No interim analyses will be performed unless explitly required by the DSMB with a strong rational. The process for communicating the report is as follow:

- The data officer will extract unblinded data and prepare reports for the DSMB (using the attached shell) and disseminate the report one week prior to the scheduled meeting.
- The data officer will be responsible for extracting both confidential and non-confidential data from the trial data collection platform.
- The data officer will participate in the DSMB meetings to take the members through the report if required.
- These discussions will remain confidential and not communicated to the trial team.

Responsibilities of the Chief Investigator and Trial Streering Group (TSG)

- The trial leads and trial manager must be available to attend open sessions.
- Other TSG members (see membership details on p. 5) are not required to attend, but may attend if they wish to.

**Safety Analyses**

Safety analyses are:

- Suicidal ideation, as measured by:
- % scoring >20 on the SIDAS
- A recent suicide attempt (identified at post-intervention or follow up survey via Q “Have you attempted suicide in the past 30 days?’ or ad hoc self report by participants to research study email)
- Serious adverse events (including all hospitalisations and deaths).
- Enrollment data, intervention completion data, attrition data, adverse event data, and other administrative data.

The TSG cannot access the unblinded data for suicidal ideation or attempt as these are outcome measures and will be shared only in a closed session.

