## 6.2. Secondary outcome measures

**Suicide Behaviours**

Participants’ previous suicide attempts and self-injury are assessed by eight questions developed for a previous suicide prevention trial [23]. Participants are invited to indicate whether they have attempted suicide in their lifetime and in the past 30 days on a three-point Likert scale, ranging from ‘No, never (0)’, ‘Yes, once (1)’, to ‘Yes, more than once (2)’. They are also asked to report the number of suicide attempts over their lifetime, and the number of months that they have been thinking about suicide. Apart from that, participants are asked to indicate whether they have intentional self-injury in their lifetime on the aforementioned three-point Likert scale. If yes, they are asked to provide the number of times of their intentional self-injury and rate the severity of the worst injury in the past month on a three-point Likert scale, ranging from ‘No care was needed (1)’, ‘Some care was needed (2)’, to ‘Required medical care (3)’.

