## 6.5. Assessment schedule

Data will be collected at baseline (day 0), post-intervention (day 42), and 4-month follow-up (day 182).The Table below describes the timing of each measure. All survey questions/items are described in Appendix C.

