**Suicidal Ideation Attributes Scale (SIDAS)**

**Now we’re going to ask you some questions are about your suicidal thoughts, and the severity of them.**

**Please think about the past month when answering the following questions.**

##

| In the past month, how often have you had thoughts about suicide? | | | | | | | | | | |
| --- | --- | --- | --- | --- | --- | --- | --- | --- | --- | --- |
| 0  Never | 1 | 2 | 3 | 4 | 5 | 6 | 7 | 8 | 9 | 10  Always |
| In the past month, how much control have you had over these thoughts? | | | | | | | | | | |
| 0  No control | 1 | 2 | 3 | 4 | 5 | 6 | 7 | 8 | 9 | 10  Full control |
| In the past month, how close have you come to making a suicide attempt? | | | | | | | | | | |
| 0  Not close | 1 | 2 | 3 | 4 | 5 | 6 | 7 | 8 | 9 | 10  Made an attempt |
| In the past month, to what extent have you felt tormented by thoughts about suicide? | | | | | | | | | | |
| 0  Not at all | 1 | 2 | 3 | 4 | 5 | 6 | 7 | 8 | 9 | 10  Extremely |
| In the past month, how much have thoughts about suicide interfered with your ability to carry out daily activities, such as work, household tasks or social activities? | | | | | | | | | | |
| 0  Not at all | 1 | 2 | 3 | 4 | 5 | 6 | 7 | 8 | 9 | 10  Extremely |

**We’d just like to ask you a few more questions about prior self-harm behaviour. Just to remind you, these questions are completely voluntary.**

| **What the user will see** | | **Drop down response options available** |
| --- | --- | --- |
| Have you ever attempted suicide? | --- select ---- | No, never Yes, once  Yes, more than once |
| If more than once, how many times? | --- select ---- | 2  3  4  5  6+ |
| How many months have you been thinking about suicide? | --- select ---- | 1 or less  2  3 to 6  >6 to 12  >12 to 24  >24 to 36  >36 |
| How often, on average, do you think about suicide? | --- select ---- | Daily Weekly Monthly  Less than monthly |
| Have you attempted suicide in the past 30 days? | --- select ---- | No, never Yes, once  Yes, more than once |
| Have you ever injured yourself on purpose (i.e., intentional, self-inflicted damage to the surface of the body without suicidal intent) | --- select ---- | No, never  Yes, once  Yes, more than once |
| In the past month, how often have you injured yourself on purpose? | - If ‘Yes, more than once’ then select - | 2-5 times (low)  6-9 times (moderate)  10-20 times (high)  20+ times (severe) |

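### The 30-day suicide-attempt question covers only 60 days of follow-up, and the past-month self-injury item cannot record zero or one episode

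*Protocol*

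**What the plan says.** **Attempts.** Appendix E, Safety Analyses, lists "A recent suicide attempt (identified at post-intervention or follow up survey via Q". The question meant is the Appendix C item "Have you attempted suicide in the past 30 days". The same line adds "ad hoc self report by participants to research study email", and the next adds "Serious adverse events (including all hospitalisations and deaths". Section 6.2 makes suicide behaviours a secondary outcome and says participants report "whether they have attempted suicide in their lifetime and in the past 30 days", along with a lifetime count. In Appendix C that count runs 2, 3, 4, 5, 6+.

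**Timing.** Section 6.5 states "Data will be collected at baseline (day 0), post-intervention (day 42), and 4-month follow-up (day 182". Section 1.1, Section 5.2 and the DSMB charter place the last survey three months after the intervention. Section 3.1 and the survey schedule table say four months.

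**Schedule.** The table has no row for the suicide-behaviour items. Suicide attempt is named only in the PHQ-9 row, which is marked at all three surveys. The PHQ-9 printed in Appendix C has no attempt question; its last item concerns thoughts.

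**Self-injury.** Appendix C first asks about lifetime self-injury (never, once, more than once). The follow-on "In the past month, how often have you injured yourself on purpose" is shown only to those answering more than once and offers 2–5, 6–9, 10–20 and 20+. The worst-injury item for the past month goes to those answering once or more than once and offers mild, moderate or severe. Section 6.2 instead says the number of times is asked of anyone who answers yes.

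**The concern.** In a trial of people with suicidal ideation, attempts are both a secondary outcome and a main safety count. A 30-day question asked at day 42 and again months later leaves gaps: days 0 to 12, which include first exposure to the app, and the stretch from day 42 to 30 days before T2. An attempt in a gap reaches the safety count only if the participant writes in unprompted or it meets the SAE definition.

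The self-injury frequency item has a different fault. A participant who has self-injured before but stopped during the trial has no true answer, so the item cannot show the improvement the app might produce. Events that were never asked about, and answers that could not be given, cannot be restored by any later analysis.

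**Working it through.** The plan gives no coverage figure of its own, so there is none to reproduce.

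**Inputs.** Recall is 30 days (Appendix C; Appendix E, Safety Analyses). T1 is day 42 (Section 6.5). T2 is three months after T1 (Sections 1.1 and 5.2, Appendix E), four months after T1 (Section 3.1, schedule table) or day 182 (Section 6.5). Day 182 is 182 − 42 = 140 days after T1, which matches neither.

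**Attempt windows.** The question at T1 reaches back to day 12, and at T2 to day T2 − 30. The earliest reading of T2 is day 126, and 126 − 30 = 96 is later than 42, so the windows never overlap. Covered time is 30 + 30 = 60 days.

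Days outside = 12 + (T2 − 30 − 42) = T2 − 60. Share outside = (T2 − 60) / T2.

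The last column supposes that the week-3 safety check (Section 12.1, about day 21) includes SIDAS item 3, which has past-month recall and a top anchor for having made an attempt, and that the answer is used. Days 0 to 42 are then covered and the gap is T2 − 72.

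| Reading of T2 | T2 day | Days outside | Share | With SIDAS item 3 at week 3 |
|---|---|---|---|---|
| 12 weeks after T1 | 126 | 66 | 52.4% | 54 (42.9%) |
| 91 days after T1 | 133 | 73 | 54.9% | 61 (45.9%) |
| 92 days after T1 | 134 | 74 | 55.2% | 62 (46.3%) |
| 4 months (120 days) | 162 | 102 | 63.0% | 90 (55.6%) |
| 4 months (122 days) | 164 | 104 | 63.4% | 92 (56.1%) |
| Day 182 as written | 182 | 122 | 67.0% | 110 (60.4%) |

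Within the six-week treatment period the definition misses 12/42 = 28.6% of days.

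**Other routes.**
- SIDAS item 3 at T1 and T2 has past-month recall, so it repeats the same windows.
- An SAE under Section 10.3 requires death, life-threatening illness or injury, permanent impairment, hospitalisation, or intervention to prevent such outcomes. An attempt with none of these does not qualify.
- The lifetime count is exact up to 5 and capped at 6+. If repeated, its change from baseline would show new attempts in anyone below the cap. Appendix E does not use it.

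**Self-injury items, by true state.**

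| Lifetime answer | Past-month truth | Frequency item | Worst-injury item |
|---|---|---|---|
| Once | 0 | not shown | no true option |
| Once | 1 | not shown | can be answered |
| More than once | 0 | no true option | no true option |
| More than once | 1 | no true option | can be answered |
| More than once | 2 to 19 | can be answered | can be answered |
| More than once | exactly 20 | two options fit | can be answered |
| More than once | over 20 | can be answered | can be answered |

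The gate at more than once also contradicts Section 6.2, which asks the number of anyone answering yes.

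**The case against.** The charter defines a recent attempt, so a 30-day window may be deliberate, and Section 6.2 says the items come from an earlier suicide prevention trial. Both arms have the same windows, so the window by itself favours neither arm, and days 12 to 42 take in 30 of the 42 treatment days. These points stand. They mean the problem is lost events, not a built-in bias between arms.

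Several stronger readings are tempting, and the documents do not support them:

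- *More than half of follow-up is unobserved, with 55% as a floor.* A 12-week reading gives 52.4%. Email reports, SAEs and possibly SIDAS item 3 at week 3 also capture some events. The time is outside systematic recall, not unobserved.
- *The same share of attempts is missed.* That needs a constant attempt rate, which nothing in the protocol supports.
- *Attempts are not scheduled at all.* The table names suicide attempt at all three surveys, but under an instrument that has no such question.
- *The DSMB would see an inflated self-harm rate.* The DSMB Meetings section gives "aggregate data indicates self-harm above the rates expected from this group" as an example of a reason to unblind, but does not tie it to this item. Neither the safety analyses nor the list of closed-session data includes self-injury. Appendix C says the items are voluntary, so someone with no true option may leave a blank. Not asking single-episode respondents works in the opposite direction from forcing 2–5.

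**Conclusion.** The concern holds in two parts.

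First, the attempt measure named for the safety analyses covers 60 days. Under every stated timing of T2, more than half of follow-up falls outside its recall. The spread from 52% to 67% comes from the protocol's own disagreement about T2. If SIDAS item 3 is in the week-3 check and is used, the three-month figure falls to about 43% to 46%, and the gap after T1 remains. Whether that screener contains item 3 is an assumption, since Section 12.1 does not say.

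Second, the past-month self-injury items cannot record none, and the frequency item cannot record one. This is a plain fault in the response options and needs no assumption. It may show up as wrong categories or as blanks, so neither its size nor its direction can be stated.

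**What to change.** - At T1 and T2, ask every participant how many suicide attempts, and how many self-injury episodes, they have had since the last survey, with options 0, 1, 2–5, 6–9, 10–20 and more than 20.
- Keep the 30-day attempt item for comparability. Use the since-last-survey attempt count in the DSMB report.
- Add 0 and 1 to the past-month self-injury frequency item, remove the overlap at 20, and add a none option to the worst-injury item. Bring the Appendix C gate into line with Section 6.2.
- Give the suicide-behaviour items their own row in the schedule table and take suicide attempt out of the PHQ-9 row.
- Reconcile the T2 timing across Sections 1.1, 3.1 and 6.5 and the schedule table.

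The cost is two added questions, corrected response options and a minor ethics amendment. The real downside is recall: at T2 the new items look back 84 to 140 days (126 − 42 to 182 − 42) instead of 30. Keeping the 30-day attempt item limits that loss.
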